## Abstract

**Introduction:**

Minimally invasive liver surgery (MILS), such as laparoscopic and robotic hepatectomy, has been developed and is an effective alternative to traditional open hepatectomy. Although surgical techniques and postoperative management have improved, many institutions continue to perform routine postoperative abdominal drainage. In open hepatectomy, abdominal drainage after uncomplicated hepatectomy increases overall and wound-related complications without a reduction in the risk of intra-abdominal fluid collections that require intervention. The aim of this study was to elucidate the feasibility of non-routine abdominal drainage for patients who undergo MILS for tumors located outside the posterosuperior area.

**Methods and analysis:**

This study is a multicenter randomized controlled trial and will recruit 182 patients who undergo MILS. The study duration is three years, including a 2-year registration duration. Participants will be randomly assigned to either the non-routine drainage group or the routine drainage group (ratio 1:1) to prove non-inferiority. The primary study outcome is the incidence of in-hospital postoperative complications of Clavien–Dindo grade ≥ II. The secondary study outcomes are length of postoperative hospital stay, incidences of specific postoperative complications and all postoperative complications, and surgery-related mortality.

**Ethics and dissemination:**

Ethical approval has been obtained from the institutional review board (No. 20232008). The results of this study will be published in international peer-reviewed journals.

## Introduction

Although the outcomes of other treatment modalities, mainly chemotherapy with or without immune checkpoint inhibitors, have recently improved, surgical hepatic resection for liver tumors, including hepatocellular carcinoma, colorectal liver metastases, and cholangiocarcinoma, remains the cornerstone of the treatment strategy^[1-4]^. Curative liver resection for a primary or metastatic liver tumor could lead to a favorable long-term prognosis after surgery^[5,6]^. Moreover, early recovery from surgical invasiveness is considered important and is the basis for the common use of enhanced recovery after surgery protocols[7].

To reduce physical damage and to accelerate postoperative recovery, minimally invasive liver surgery (MILS), such as laparoscopic and robotic hepatectomy, has been developed and is an effective alternative to traditional open hepatectomy. Several studies have reported that MILS for minor or major liver resection resulted in both short- and long-term oncological favorable outcomes^[4,8,9]^.

Although surgical techniques and postoperative management have improved, it is presumed that many institutions continue to perform routine abdominal drainage to facilitate early diagnosis of postoperative bleeding or bile leakage, and to potentially prevent intra-abdominal fluid collections^[10,11]^. Notably, early drain removal after hepatectomy has been included in enhanced recovery after surgery guidelines and may be associated with faster recovery and reduced length of hospital stay[12]. In open hepatectomy, seven randomized controlled trials (RCTs)^[13-19]^ and a meta-analysis of these RCTs[20] have been published. The meta-analysis found that abdominal drainage after uncomplicated hepatectomy increased overall and wound-related complications without a reduction in the risk of intra-abdominal fluid collections that required intervention[20]. On the other hand, there has been no RCT in MILS.

## Objective

The objective of this multicenter randomized comparative study is to elucidate the feasibility of non-routine abdominal drainage as non-inferiority for patients who undergo MILS for primary or metastatic liver tumors located outside the posterosuperior area.

## Methods and analysis

### Study design

This study is an RCT (1:1 ratio) in which eligible patients who meet the inclusion criteria will be enrolled and randomly assigned to either the non-routine abdominal drainage group or the routine abdominal drainage group after providing consent. The randomization will be performed using UMIN Internet Data and Information system for Clinical and Epidemiological research, Cloud version with minimization method and assignment factors are institution, diagnosis (primary liver tumor/metastatic liver tumor), and surgical procedure (partial hepatectomy/subsegmentectomy/left lateral segmentectomy). MILS will be performed by laparoscopy or robotic hepatectomy. This is a non-inferiority study to confirm the efficacy and safety of non-routine abdominal drainage compared with routine abdominal drainage in patients who undergo MILS, including S2, S3, S4, S5, and S6 partial hepatectomy; S3, S5, and S6 subsegmentectomy; and left lateral segmentectomy. This study conforms to the CONSORT criteria. The study duration is three years, including a 2-year registration duration.

## Endpoints

Primary study outcome:

Incidence of in-hospital postoperative complications of Clavien-Dindo grade ≥ II resulting from MILS including resulting from drainage.

Secondary study outcomes:
Length of postoperative hospital stay;Incidence of specific postoperative complications (i.e. biliary leakage, postoperative bleeding, massive ascites, massive pleural effusion, surgical site infection);Incidence of all postoperative complications;Surgery-related mortality.

## Patient eligibility

Inclusion criteria: Patients who meet all of the following criteria will be eligible:
Primary or metastatic liver tumors that are eligible for laparoscopic hepatectomy or robot-assisted laparoscopic hepatectomy at the participating institution from the date of study approval;S2, S3, S4, S5, or S6 partial hepatectomy; S3, S5, or S6 subsegmentectomy; or left lateral segmentectomy as the surgical procedure;Eastern Cooperative Oncology Group performance status grade 0–1;Patients who have received a full explanation of the study and provide their free and voluntary consent based on their full understanding of the study.

Exclusion criteria: Patients will be excluded if they meet any of the following criteria:
Complicated resection of other organs, excluding the gallbladder;Serious comorbidities;Did not agree to participate in the study after receiving a full explanation of the study;Deemed inappropriate for inclusion by the investigator.

## Surgical procedures

All participating centers are high-volume centers for hepatobiliary and pancreatic surgery. The treating surgeons at all participating centers are beyond their learning curves for performing MILS. The surgical procedure, selection of robotic or laparoscopic hepatectomy, extent of hepatic resection, and the method of hepatic parenchymal transection (clamp-crushing method or Cavitron ultrasonic surgical aspirator), will be determined by each investigator in accordance with their institutional criteria. In the routine drainage group, after completion of liver resection, a single silicone drain will be placed under the cut surface of the liver, or in the subphrenic space or Winslow’s foramen at the end of surgery; the other end will be pulled through a skin incision and connected to a closed bag with suction. The drain will be removed in accordance with each institution’s criteria depending on the amount of drainage, without bile leakage findings (the International Study Group of Liver Surgery definition[21]). On the contrary, in the non-routine group, after completion of liver resection, the abdomen is closed without insertion of a silicone drain, and the operation is terminated.

## Data collection

This study will examine and collect the information listed below and in Table 1. Blood tests and abdominal contrast-enhanced computed tomography (CT) will be routine procedures performed to collect standard information, as in regular medical care.
Patient background information: sex, age, body mass index, primary disease, liver function prior to surgery, surgical history;Surgical factors: surgical procedure, duration of surgery, blood loss, duration of the Pringle maneuver, pathological liver fibrosis;Blood tests: hematological indices, liver function indices, kidney function indices;Ascites biochemical testing: bilirubin level in the drainage fluid, including new punctures;Complications: presence of postoperative complications and which ones;Abdominal contrast-enhanced CT to evaluate fluid collections or other radiological findings.

**Table 1 T1:** Information that will be collected in this study

Factors	Prior to surgery	Following surgery	Observation period following surgery		Upon discontinuation
Period	0-4 weeks before	0 weeks	1 week following surgery	At discharge	Upon discontinuation
Medical checkup	○	–	○	○	○
Obtainment of consent	○	–	–	–	–
Random allocation	●	–	–	–	–
Patient background	○	–	–	–	–
Surgical factors		○			
Blood test	○		○	○	○
Ascites biochemical test	–	–	○	○	○
Regarding complications	–	–	○	○	○
Abdominal contrast-enhanced CT	○	–	○	–	○

CT, computed tomography.

## Sample size

The primary endpoint of the study is the incidence of postoperative complications of Clavien–Dindo grade ≥ II resulting from hepatic resection, in the full analysis set (FAS). A meta-analysis of open hepatectomy with and without routine abdominal drainage showed that the rate of postoperative complications of Clavien–Dindo grade ≥ II was 36.1% in the routine drainage group, 26.6% in the non-routine drainage group, and 32.6% in all patients[22]. Additionally, the odds ratio for postoperative complications associated with MILS versus open hepatectomy was approximately 0.5[23]. The anticipated complications rates for MILS in this study are 20% in the routine drainage group and 15% in the non-routine drainage group. Although the overall complications rate in a study of non-routine drainage in open hepatectomy was 32.6%[22], it is clear that the complications rate for MILS is lower than that for open hepatectomy, and the complications rate with non-routine drainage in MILS should be lower than that for open hepatectomy. Therefore, it is considered clinically acceptable if the complications rate in the non-routine drainage group is no more than 10% higher than that in the routine drainage group. Therefore, we set the non-inferiority margin at 10%, and calculated the required number of patients for each group as 82, assuming a one-sided alpha error of 5% and a power of 80%. Considering an expected dropout rate of approximately 10%, we set the target number of patients at 182 in total (91 cases per group).

## Analysis set

FAS: Patients who have received all or part of the protocol treatment, excluding ineligible patients, and patients who have undergone at least one efficacy evaluation. However, patients who are found ineligible after enrollment will be excluded.

Per protocol set: Patients included in the FAS who are not in serious non-compliance with the study protocol.

Safety set: The group of patients for whom some or all of the protocol treatment has been administered.

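### The primary analysis set excludes patients found ineligible after enrolment without limiting this to facts that existed before randomisation, so events or arm-aware judgements at operation can remove randomised patients

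*Protocol article*

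**What the plan says.** All references are to the protocol article.

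- **Primary set.** The Sample size section places the primary endpoint, complications of Clavien–Dindo grade II or higher, in the FAS.
- **FAS definition (Analysis set).** It begins "FAS: Patients who have received all or part of the protocol treatment, excluding ineligible patients", adds "patients who have undergone at least one efficacy evaluation", and then repeats the eligibility condition: "However, patients who are found ineligible after enrollment will be excluded".
- **Other sets (Analysis set).** The per protocol set is the part of the FAS without serious non-compliance. The safety set is everyone given some or all of the protocol treatment.
- **Timing of allocation.** Under Study design, patients "will be enrolled and randomly assigned to either the non-routine abdominal drainage group or the routine abdominal drainage group after providing consent". Table 1 marks random allocation in the pre-surgery column, 0–4 weeks before. Surgical procedure is one of the minimisation factors.
- **Eligibility (Patient eligibility).** Inclusion requires one of a named list of resections. Exclusions include "Complicated resection of other organs, excluding the gallbladder" and a patient whom the investigator considers unsuitable.
- **What separates the arms (Surgical procedures).** In the non-routine group, after resection, "the abdomen is closed without insertion of a silicone drain, and the operation is terminated".

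**The concern.** In a randomised comparison, an exclusion from the primary set is harmless if it depends only on facts fixed before allocation and is judged without knowledge of the arm. The FAS rule requires neither. Ineligibility may come to light at any time after enrolment, and three of the criteria are open to reassessment once the operation has begun: which resection is done, whether another organ is resected, and whether the investigator thinks the patient suitable. The person best placed to make that reassessment is the surgeon, who must know the arm by closure at the latest because the arm decides whether a drain goes in. The article does not use the word open; this follows from the nature of the intervention.

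Patients whose operation departs from plan may well carry a higher complication risk. If they leave one arm more than the other, the two groups being compared are no longer the randomised ones. A shift of one or two points in the risk difference matters against a margin of 10 points with about 82 to 91 patients per arm.

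**Working it through.** **1. The plan's own sample size.** Inputs from Sample size: 20% routine, 15% non-routine, margin 10 points, one-sided alpha 5%, power 80%. The distance to the margin is 0.10 − (0.15 − 0.20) = 0.15. With the Farrington–Manning method, the rates restricted to the null are 0.2403 and 0.1403.

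- Null variance: 0.2403 × 0.7597 + 0.1403 × 0.8597 = 0.3032
- Alternative variance: 0.15 × 0.85 + 0.20 × 0.80 = 0.2875
- n = (1.645 × √0.3032 + 0.842 × √0.2875)² / 0.15² = 81.84, so 82 per group, as stated

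The dropout step, 82 × 1.1 = 90.2, gives the stated 91 per group. The allowance is 182 − 164 = 18 patients. The sample size is not in question here.

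**2. Can another set stand in for all randomised patients?** The per protocol set lies inside the FAS, so it cannot restore anyone. The safety set carries no stated ineligibility exclusion, but it requires treatment to have been given and the primary test is not tied to it. Neither is defined as all randomised patients.

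**3. Illustration of size.** The removal fractions and risks below are assumptions; the article gives none. True rates are set at the margin, 20% routine and 30% non-routine, with n = 82 per arm. A fraction f with complication risk r is removed.

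- Rate left in the non-routine arm: q = (0.30 − f·r)/(1 − f)
- Rate left in the routine arm: c = 0.20 if untouched, or (0.20 − f·r)/(1 − f) if the same removal occurs there
- False non-inferiority rate = Φ[(0.10 − (q − c))/SE − 1.645]
- SE² = q(1 − q)/(82(1 − f)) + c(1 − c)/m, where m = 82, or 82(1 − f) if removal is in both arms

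Central case, f = 8%, r = 50%, non-routine arm only: q = (0.30 − 0.04)/0.92 = 0.2826; SE = √(0.2027/75.44 + 0.16/82) = 0.0681; Φ(0.0174/0.0681 − 1.645) = Φ(−1.39) = 8.2%.

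Same removal in both arms: c = (0.20 − 0.04)/0.92 = 0.1739; difference 0.1087; SE = 0.0678; Φ(−0.0087/0.0678 − 1.645) = Φ(−1.77) = 3.8%.

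| f, r | Non-routine rate falls by | False non-inferiority, one arm | False non-inferiority, both arms |
|---|---|---|---|
| 5%, 40% | 0.5 points | 5.9% | 4.3% |
| 8%, 50% | 1.7 points | 8.2% | 3.8% |
| 10%, 60% | 3.3 points | 12.4% | 3.5% |

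Starting from 91 per arm, the one-arm figures are 5.9%, 8.4% and 13.0%. Equal removal widens a true 10-point difference to 10/0.95 = 10.5 points or 10/0.90 = 11.1 points, which works against non-inferiority.

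**4. How few patients can decide the result.** A simple unadjusted 90% interval is used here; the plan's interval is stratified. With 20/91 non-routine and 18/91 routine, the difference is 2.2 points and the upper limit is 0.022 + 1.645 × 0.0602 = 12.1%, which fails. Take out three non-routine patients with events: 17/88 against 18/91 gives −0.0046 + 1.645 × 0.0593 = 9.3%, which passes.

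**5. Cost in power of keeping everyone.** With 91 per arm and the plan's own rates, Φ[(0.15 − 1.645 × √(0.3032/91))/√(0.2875/91)] = 83.6%, against 80.1% at 82.

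**The case against.** Four arguments count against the point.

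*Drain crossovers.* A reader might infer that a non-routine patient who is given a drain counts as untreated and is dropped, while the matching routine patient stays. The text does not support this. The FAS keeps anyone who had all or part of the protocol treatment, and a patient whose liver was resected most naturally had part of it. Because the per protocol set removes serious non-compliance from within the FAS, non-compliant patients must be in the FAS to begin with. This objection stands; at most, what counts as part of the treatment needs defining.

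*Planned or actual procedure.* A reader might also infer that eligibility is settled by what happens in surgery. The article does not say so. Procedure is a minimisation factor at an allocation made before surgery, so the procedure used there must be the planned one, and the other-organ criterion can be read the same way. This stands as a reading. But the FAS rule does not say which is meant, and the investigator criterion is discretionary on either reading.

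*Direction.* Drain placement follows completion of the resection, and nothing in the article suggests that changes of resection differ by arm. Equal removal works against non-inferiority. This stands, and it limits the conclusion.

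*Condensed article.* Who judges late ineligibility, and when, is often left to the full protocol. That is fair for the procedure of adjudication. It does not cover the exclusion itself, which the article states as a rule and leaves unrestricted.

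**Conclusion.** The defect is the unrestricted exclusion of patients found ineligible after enrolment from the set that carries the primary test, in a trial allocated before surgery and operated on by surgeons who must know the arm. The article permits removal of randomised patients through later events or arm-aware judgement and defines no all-randomised set to check the result against.

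It would go too far to say that the plan is biased towards non-inferiority. That needs removal mainly from the non-routine arm, which the documents allow but do not show. The rise from 5% to about 6–12% rests wholly on assumed one-arm removal of 5–10% at 40–60% risk; with equal removal in both arms the rate falls to about 3.5–4.3%. The number of patients affected cannot be derived from the article.

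This should be fixed; confidence is moderate.

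**What to change.** Reword the Analysis set section:

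- Define the primary FAS as all randomised patients who undergo liver resection, analysed in the allocated arm.
- Allow exclusion for ineligibility only on facts that existed before randomisation, judged blind to arm and outcome.
- State that intraoperative changes of procedure, conversion and drain placement against allocation stay in the FAS and leave only the per protocol set. For drains, the present wording already points this way.
- Report all exclusions, including patients not resected, by arm and with reasons. Report the per protocol result beside the FAS result.

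The cost is wording only: no new data and no extra patients. The downside is that a few non-adherent patients remain in the primary analysis, which the per protocol result helps to assess. Requiring resection is still a condition met after randomisation, which is why the by-arm count of patients not resected is needed.

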## Statistical analysis

The non-inferiority of the primary study endpoint between the non-routine abdominal drainage and routine abdominal drainage groups will be met if the upper limit of the 90% confidence interval for the risk difference, calculated using the Cochran–Mantel–Haenszel method with allocation-adjusting factors as covariates, is within the non-inferiority margin of 10%. No interim analyses are planned.

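### The non-inferiority decision rests on the full analysis set, and the per-protocol set has no stated part in it, so drains placed against allocation can ease a claim about omitting the drain

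*Protocol article*

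**What the plan says.** Under Sample size, the primary endpoint is the rate of Clavien–Dindo grade II or higher complications "resulting from hepatic resection, in the full analysis set (FAS"). Under Statistical analysis, non-inferiority "will be met if the upper limit of the 90% confidence interval for the risk difference" lies within 10%. That sentence names no analysis set and adds no further condition.

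Under Analysis set, the FAS is made up of treated, eligible patients with at least one efficacy evaluation. How a patient drained against allocation is counted is not mentioned. The per-protocol set is "Patients included in the FAS who are not in serious non-compliance with the study protocol". No section of the article says what is done with it.

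Table 1 places random allocation in the weeks before surgery. Under Surgical procedures, the non-routine arm is defined at the end of resection: "the abdomen is closed without insertion of a silicone drain".

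**The concern.** The arm is fixed before the surgeon sees the cut surface. The Discussion gives the usual reasons for a drain as bile leakage, bleeding and ascitic fluid, and some of these can show themselves in theatre. A patient allocated to no drain may therefore leave theatre with one. In the FAS that patient counts towards the no-drain arm while having had the control treatment. When crossover is unrelated to risk, this pulls the two observed rates together. In a superiority trial that costs power. In a non-inferiority trial whose true difference lies at the margin, it helps the claim.

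Under the rule as stated, an FAS result inside the margin is a success whatever the per-protocol set shows. The Discussion intends the result to help surgeons decide whether to place a drain, so many readers will take it as evidence about leaving the drain out. For that question the nominal 5% may not hold.

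**Working it through.** **Inputs from the article.** One-sided alpha 5%, power 80%, margin 10 percentage points, 1:1 allocation. "The anticipated complications rates for MILS in this study are 20% in the routine drainage group and 15% in the non-routine drainage group". The authors "calculated the required number of patients for each group as 82" before dropout.

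**Reproducing the plan's figure.** The event is adverse, so the distance from the expected difference to the margin is 0.10 + 0.05 = 0.15. The Farrington–Manning formula uses null-restricted rates of 24.0% and 14.0%:

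n = [1.645 × √(0.240×0.760 + 0.140×0.860) + 0.842 × √(0.15×0.85 + 0.20×0.80)]² / 0.15² = 81.84, so 82.

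This matches. Dropout: 82 / 0.9 = 91.1, against 91 stated for approximately 10%. The sample size is not in question.

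**Assumptions that are not in the article.** The crossover rate c among patients allocated to no drain is taken as 0% to 20%. The true rates are put at the margin: 20% drained, 30% undrained. To begin with, crossover is unrelated to risk, and a crossed-over patient takes the rate of the treatment received.

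**Dilution in the FAS.** Rate in the no-drain arm = 0.20 + 0.10 × (1 − c); routine arm = 0.20. Error = probability that the upper 90% limit falls below 0.10, by exact binomial enumeration, unstratified, 82 per group.

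| c | Difference in FAS | Wald interval | Farrington–Manning |
|---|---|---|---|
| 0% | 10.0 points | 5.2% | 5.1% |
| 5% | 9.5 points | 6.0% | 5.9% |
| 10% | 9.0 points | 7.0% | 6.9% |
| 20% | 8.0 points | 9.2% | 9.1% |

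Hand check at c = 10%: SE = √(0.29×0.71/82 + 0.20×0.80/82) = 0.0668, and Φ(0.01/0.0668 − 1.645) = Φ(−1.495) = 6.7%, close to the exact value.

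**Requiring both sets, crossover unrelated to risk.** By simulation with the Wald rule, the joint error is about 4.8% at c = 10% and at c = 20%.

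**Crossover related to risk.** Let 10% of patients have r times the risk of the others, let these be the ones drained against allocation, and let the drain effect be multiplicative. The same kind of patient stays in the routine arm. For r = 2, the lower-risk multiplier is 1/(0.9 + 0.1×2) = 0.909 and the higher is 1.818.

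- FAS, no-drain arm: 0.9 × 0.30 × 0.909 + 0.1 × 0.20 × 1.818 = 0.282, a difference of 8.2 points.
- Per-protocol set, no-drain arm: 0.30 × 0.909 = 0.273, a difference of 7.3 points, because the high-risk patients leave one arm only.

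| r | FAS alone | Per-protocol alone | Both required |
|---|---|---|---|
| 1 | 7.0% | 5.3% | 4.8% |
| 1.5 | 7.9% | 7.9% | 6.4% |
| 2 | 8.8% | 11.1% | 7.9% |

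With a constant 10-point drain effect instead, r = 2 gives 6.7% for the FAS and 8.4% for the per-protocol set (normal approximation). The ordering is the same.

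**Power at the planning rates.** With c = 10%, the no-drain arm has 0.15 + 0.05 × 0.10 = 15.5%. Power is about 79% for the FAS alone and 76% for both. Without crossover, and with no other serious non-compliance, the two sets coincide and nothing is lost (about 82% by the Wald rule).

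**The case against.** The strongest reply is that the trial compares two policies, routine and non-routine drainage, as allocated. For the effect of the policy, drains placed against allocation are part of what is compared, and an FAS analysed as randomised keeps its nominal 5% whatever the crossover. This stands. A reader might infer that the plan's error rate is above 5%. The documents do not support that: the excess arises only if the target is the effect of omitting the drain, and only if crossover happens. No rate is given, and the trial is limited to restricted resections by experienced surgeons at high-volume centres, which gives no particular reason to expect the upper end of the range.

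A reader might also infer that the per-protocol set will play no part at all. That goes too far. This is a condensed article, and a supporting per-protocol analysis may stand in the full protocol or analysis plan. What remains is narrower: the published success rule is sufficient on its own terms, and a merely supportive analysis elsewhere would not alter it.

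Finally, an FAS analysis with a supportive per-protocol analysis is a recognised design, and the per-protocol set can itself be biased. Both points are fair. The second is why that set should be added to the FAS and not replace it.

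**Conclusion.** The concern holds in conditional form. The article ties the decision to the FAS and gives its per-protocol set no stated part in it, while allocation before surgery leaves room for crossover. For the effect of omitting the drain, the one-sided error would be about 6% to 9% under assumed one-way crossover of 5% to 20% unrelated to risk, at 82 per group and 20% against 30%. With full adherence, or for the allocated policy, it stays at about 5%.

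It is tempting to say that a joint rule restores 5%. It does so only when crossover is unrelated to risk. Drains placed because of what is seen in theatre would be related to risk, and then the joint rule lowers the error without restoring it. Because it only adds a condition, it can never have a higher false-claim rate than the FAS rule alone.

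**What to change.** Amend the rule under Statistical analysis so that non-inferiority is concluded only if the upper limit of the 90% confidence interval is below 10 points in both the FAS, analysed as randomised, and the per-protocol set. Under Analysis set, state that a drain in the non-routine group, or none in the routine group, counts as non-compliance for the per-protocol set, and that membership is fixed before outcomes are reviewed. Since both must succeed, alpha needs no adjustment.

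The cost is a few sentences, one further run on a set already defined, and about three points of power at 10% one-way crossover. Report the number of patients drained against allocation in each arm, so that readers can judge how far the two sets may differ.
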